# Resistance training combined with blood flow restriction in cirrhosis: study protocol for a randomized controlled trial

**DOI:** 10.1186/s13063-020-04410-2

**Published:** 2020-05-29

**Keywords:** End stage liver disease, Sarcopenia, Physical activity, Muscle strength, Quality of life, Hypertrophy

## Abstract

**Background:**

Patients affected by hepatic cirrhosis show reductions in muscle mass and function, with poor quality of life and functional performance. As such, resistance training with blood flow restriction (BFR-RT) could be a useful therapeutic tool for health promotion. Thus, we aim to verify the effects of this intervention on muscle strength, muscle mass, fiber Pennation angle, fascicle length, functional performance, quality of life, and fall risk scores in this population.

**Methods:**

Thirty participants will be randomly distributed between 1) BFR-RT and 2) control (CTRL). Assessments will occur at three time points: before the training intervention (0 W), after 12 weeks (12 W), and at follow-up (24 W). The following variables will be assessed: Child-Pugh classification; MELD score; SF-36 questionnaire; fatigue severity index; 6-min walk test; timed-up and go; 30-s sitting and rising test; dietary record; one-repetition maximum (1-RM) strength test (knee extension exercise); and vastus lateralis’ cross-sectional area, Pennation angle, and fascicle length. The BFR-RT group will undergo 12 weeks of knee extension exercise (1 × 30 repetitions and 3 × 15 repetitions at 20% 1-RM and 50% of total blood flow occlusion pressure), with two sessions per week. Data normality will be assessed using the Shapiro-Wilk test. In case of normal distribution, a one-way repeated measures analysis of variance will be implemented to test for differences in baseline values. A mixed model then will be applied for each dependent variable. In case of non-normal data distribution, a Kruskal–Wallis test will be implemented to test for differences in baseline values. Next, the Friedman test will be used to analyze repeated measures. Within- and between-group effect sizes will be calculated using Cohen’s *d* for each outcome. Finally, the minimal clinically important difference will be analyzed with distribution-based methods.

**Discussion:**

To our knowledge, this will be the first trial to investigate BFR-RT in patients with cirrhosis and evaluate the effects on neuromuscular parameters, functional performance, disease severity, and quality of life outcomes.

**Trial registration:**

Brazilian Clinical Trials Registry (ReBec): RBR-395mfw. Registered on 25 August 2018.

## Background

Liver cirrhosis (LC) is considered the final outcome of chronic liver injury and is characterized by the development of diffuse regenerative nodules enveloped in fibrous tissue and progressive hepatic dysfunction [1, 2]. Many different complications can be associated with LC. One important implication for the cirrhotic patient is sarcopenia [3], a syndrome characterized by muscle wasting and loss of muscle strength [4]. Different factors have been associated with sarcopenia onset in LC; one is the reduced physical activity level commonly observed in this population [5, 6]. As a result, sarcopenia causes even further reductions in physical activity levels, as well as reduced quality of life, decline in functional performance, increase in fall risk, development of other complications of LC (e.g., sepsis-related death, uncontrolled ascites, hepatic encephalopathy), poor outcomes after liver transplantation, and reduction in survival rate [7–9]. Thus, a physical activity program has been proposed to help attenuate sarcopenia impact in LC, ultimately improving quality of life and survival [9].

In this sense, for the general population, resistance training (RT), either at high-load (~ 80% one-repetition maximum (1-RM)) or at low-load (~ 20–30% 1-RM) to muscle failure, is well known to result in marked increases in muscle strength and mass [10], which can be accompanied by modifications in muscle architecture (e.g., fiber Pennation angle and fascicle length [11]). Additionally, improvements in functional performance [12] and quality of life [13] also have been reported. Considering sarcopenia occurrence in LC and the effects of RT on muscle strength and mass, RT could be an effective therapeutic tool in LC patients for both prevention and attenuation of sarcopenia. However, high-load RT and low-load RT to muscle failure may not be safe for the individual with LC. Even moderate exercise can increase hepatic venous pressure gradient of cirrhotic patients [14] and is associated with greater risk of variceal bleeding, impairing exercise practice.

In this sense, evidence shows that low-load RT combined with partial blood flow restriction (BFR-RT) results in significant muscle mass gains, comparable to high-load RT [15, 16] or low-load RT to muscle failure [17]. Its applicability in frail populations (e.g., elderly and cardiac patients) also has been verified, with positive outcomes after the intervention period [15, 18, 19], including functional performance [20]. Additionally, BFR-RT has been found to result in significantly smaller increases in systolic blood pressure, diastolic blood pressure and heart rate than both low-load RT and high-load RT performed to failure [21]. Thus, BFR-RT could prove to be a safe RT method in LC patients, improving muscle strength and mass while avoiding marked increases in blood pressure and, possibly, in portal pressure and variceal bleeding.

Thus, this study aims to investigate the effects of BFR-RT on muscle strength, muscle mass, fiber Pennation angle, fascicle length, functional performance, and risk of falls in LC patients. Additionally, we aim to verify whether BFR-RT is a safe method for this population. Our hypothesis is that BFR-RT will promote increases in muscle strength, muscle mass, and functional performance, while reducing the risk of falls, with no aggravation in LC condition.

## Methods/Design

This study is registered with Clinical Trials Brazil (http://www.ensaiosclinicos.gov.br), registration number RBR-395mfw. All study procedures were approved by the institution’s Ethics Committee.

### Aims

The aims of this study are as follows:
Verify the effects of BFR-RT on the knee extensor strength of LC patientsVerify the effects of BFR-RT on the vastus lateralis muscle cross-sectional area, fiber Pennation angle, and fascicle lengthVerify the effects of BFR-RT on the functional performance and risk of falls in LC patientsVerify the retention of BFR-RT effects after 12 weeks of protocol cessation (24 weeks)Verify whether BFR-RT results in adverse events in LC patients

### Design overview

This study is an experimental approach with repeated measures for data collection to investigate the efficacy and safety of a BFR-RT protocol in LC patients (Additional file 1 - SPIRIT 2013 Checklist) (Fig. 1). All participants (target *n* = 30) will be evaluated at three time points: before the training period (0 W), after 12 weeks (12 W), and at follow-up (24 W). Participants will be randomly allocated between a training (BFR-RT) and control (CTRL) group. Both groups will undergo their respective interventions two times per week for 12 weeks, followed by a no-intervention period of 12 weeks to verify the interventions carryover effects (Fig. 2).

**Fig. 1 Fig1:**
[figure not shown]
Template of recommended content for the schedule of enrollment, interventions, and assessments

**Fig. 2 Fig2:**
[figure not shown]
Design overview. Before the training period (0 W), all participants will be screened for Child-Pugh class and MELD score, as well as for quality of life, functional capacity, and risk of falls Participants will also be requested to provide a dietary record for caloric intake calculation. At least 48 h later, participants will perform a 1-RM test. Then 72 h later, vastus lateralis muscle CSA, PA, and FL will be assessed. Participants will then be randomly allocated between a training (resistance training with blood-flow restriction - BFR-RT) and control (CTRL) group. After 12 weeks of intervention (12 W), all of the previous parameters will be reassessed. A no-intervention period of 12 weeks will be carried out and, at follow-up (24 W), participants will be reassessed in order to verify the interventions carryover effects

### Setting

Recruitment will be carried out at the University Hospital and at *CAIC* (Chronic Infection Care Center). Medical records will be screened for preliminary eligibility. Participants who meet initial eligibility criteria will undergo in-person evaluation by a medic professional specialized in liver disease and will be requested to provide an informed consent before study initiation (Fig. 3). All experimental procedures will be carried out at the University Hospital.

**Fig. 3 Fig3:**
[figure not shown]
Participant recruitment steps

### Eligibility criteria

Eligibility criteria are 1) liver cirrhosis diagnosed by histopathological evaluation, hepatic elastography, or by clinic, radiologic or endoscopic criteria and 2) age ≥ 18 and ≤ 70 years. Exclusion criteria are 1) less than 6 months of alcohol abstinence, 2) MELD score > 15, 3) Child-Pugh class C, 4) decompensated chronic diseases, 5) diabetes mellitus, 6) hepatocellular carcinoma or others neoplasia, 7) previous liver transplant, 8) severe ascites, 9) persistent hepatic encephalopathy, 10) coagulation disorders characterized as INR ≥ 1.5 or platelets ≤ 75.000, or 11) medical contraindications for physical exercise practice.

### Randomization

Initially, all participants will be pooled into a single group. This group then will be organized into quartiles according to participants’ initial 1-RM and vastus lateralis CSA. Next, participants in each quartile will be allocated to either the training (BFR-RT) or control group (CTRL) using a maximally tolerated imbalance model [22]. An unpaired T test will be applied to ensure no baseline difference between groups. If significant between-groups differences are detected, the randomization procedure will be repeated until a random distribution with no significant difference is achieved. The Berger-Exner test will be performed during data analysis to verify for selection bias [23].

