## Trial status

This is version 1 of this protocol, written on July 13, 2018. Participant recruitment began in September 2018. Recruitment was expected to be completed on October 2018; however, an insufficient number of participants were recruited. Thus, recruitment is expected to be completed in July 2020. Recruitment was ongoing at the time of submission.

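### Allocation needs the whole cohort pooled and ranked before anyone is treated, but recruitment has stretched from about one month to about 22, and the article does not reconcile the two

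*Protocol article*

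**What the plan says.** The Randomization section of the protocol article gives the steps in order. First, "Initially, all participants will be pooled into a single group". Second, "This group then will be organized into quartiles according to participants’ initial 1-RM and vastus lateralis CSA". Third, "Next, participants in each quartile will be allocated to either the training (BFR-RT) or control group (CTRL) using a maximally tolerated imbalance model". An unpaired t test then compares the groups at baseline, and if it is significant, "the randomization procedure will be repeated until a random distribution with no significant difference is achieved". The target of 30 is in the Design overview.

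The Trial status section dates this as version 1, from July 2018. It reports: "Participant recruitment began in September 2018". Completion was expected in October 2018, too few people were enrolled, and now "recruitment is expected to be completed in July 2020".

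The legend to Fig. 2 gives the baseline sequence: screening, 1-RM at least 48 h later, ultrasound 72 h after that, then allocation. It mentions no holding period between the last test and allocation.

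**The concern.** Sample quartiles of a pooled group are known only when every member's value is in hand. Repeating the randomisation until the groups do not differ is possible only while everyone is still untreated. Both steps therefore assume a cohort assembled before the first training session. That is reasonable over a month. Over almost two years it is a strong demand, and the allocation text has not been adapted to the longer window.

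The two stratifying variables are also the two primary outcomes, and the training load is expressed as a percentage of 1-RM. If the 0 W values age before allocation, they no longer describe status just before training, and change from 0 W mixes the effect of the intervention with whatever happened while waiting. People who consent early may deteriorate, be transplanted or withdraw before they are allocated. If the team avoids the wait by allocating as people arrive, the reported method and the actual method differ.

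**Working it through.** **Inputs.** Target 30 (Design overview). Recruitment start September 2018, planned end October 2018, current expected end July 2020 (Trial status). Minimum gaps of 48 h and 72 h between baseline tests (Fig. 2 legend). Intervention of 12 weeks (Design overview). The article gives dates but no duration, so there is no stated figure to reproduce beyond the dates.

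**Length of the window.**
- Planned: September to October 2018 = 1 month (at most 60 days, from 1 September to 31 October).
- Current: (2020 − 2018) × 12 + (7 − 9) = 22 months.
- By day: 30 September 2018 to 1 July 2020 is 640 days; 1 September 2018 to 31 July 2020 is 699 days. Divided by 30.4375, this is 21.0 to 23.0 months.
- Relative to the intervention: 22 × 30.4375 / 84 ≈ 8 times the 12-week period.

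**Interval implied by Fig. 2.** 48 h + 72 h = 120 h, so about 5 days at the least from screening to the last baseline test, with allocation next.

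**Illustrative waits.** The article gives no accrual pattern. Assume 30 people enrolled evenly over 22 months and one allocation at the end. The wait for person i (i = 0 to 29) is 22 × (1 − i/29) months.
- Mean wait: 11 months.
- Wait above 3 months: i < 29 × 19/22 = 25.05, so 26 of 30.
- Wait above 6 months: i < 29 × 16/22 = 21.09, so 22 of 30.

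**The three ways of running it.**

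| Practice | Consequence |
|---|---|
| 0 W at enrolment, one allocation at the end | Follows the Randomization section. Departs from the Fig. 2 sequence. Earliest 0 W values up to about 22 months old at allocation |
| 0 W deferred until the cohort is full | Follows the Randomization section and Fig. 2. Earliest recruits wait up to about 22 months after consent and eligibility evaluation |
| Allocation on arrival or in batches | Follows Fig. 2. There is no single pooled group, cut-points are undefined or differ by batch, and the whole-group repeat cannot be applied |

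None of the three satisfies the allocation rule, the test sequence and the recruitment window without a cost that the article does not address.

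**The case against.** The strongest reply is that nothing in the article ties the 0 W tests to enrolment. The Setting section describes recruitment as records screening, specialist evaluation and consent, with no 1-RM or ultrasound. The Fig. 2 legend sets only a minimum gap before 1-RM. All 0 W tests could be done once the cohort is complete, which gives fresh baselines, including Child-Pugh and MELD, which are part of 0 W. This stands. A reader might infer that the primary baselines must be up to 22 months old, or that the scheme cannot be carried out at all. The documents support neither: the 22 months is an upper limit for the first recruits, holds only under testing at enrolment, and uses an expected end date. Deferral does not remove the wait, though. It moves it to the time after consent and eligibility evaluation, and eligibility items outside 0 W would age unless rechecked.

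A second reply is that ageing before a joint allocation falls equally, in expectation, on both groups, and that loss before allocation does not bias a randomised comparison. This is correct, and a reader who infers a biased treatment effect goes too far. Nor does the article show that batches were used or that anyone had been allocated by submission, so the point concerns the plan and not conduct.

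A reader might also suppose that quartiles of the two variables are crossed, giving 16 cells and 30/16 = 1.9 people per cell, too few for an imbalance limit to work. The wording points more naturally to four strata (30/4 = 7.5 each). Even with crossing, the conclusion depends on a limit that is not stated: a limit of 1 would still split a pair evenly.

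Finally, a condensed article may leave recruitment waves to the full protocol, and Figs. 1 and 3 are not shown. That would excuse silence. Here, however, the article states one pooled group and a recruitment window that sits badly with it.

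**Conclusion.** The point holds as a clash between a stated allocation rule and a stated timeline. The rule was workable for about one month of recruitment and was carried over unchanged to about 22 months (21 to 23 by day of the month). Depending on when 0 W is done, the result is old baselines for the earliest recruits, an equally long wait after consent and eligibility evaluation, or an allocation that differs from the one described. The size of the wait is a conditional upper bound; under even accrual, which is an assumption, the mean would be about 11 months.

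The cost of waiting is precision, attrition before allocation and interpretation of change from 0 W. It is not, in itself, a biased comparison between BFR-RT and CTRL. The point is worth acting on because recruitment was still open at submission and allocation cannot be redone at the analysis stage.

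**What to change.** Reconcile the Randomization section, the Fig. 2 legend and the Trial status section by amendment:

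- Replace pooled allocation with concealed sequential allocation as each participant completes 0 W. Either use maximally-tolerated-imbalance lists within a few strata whose 1-RM and CSA cut-points are fixed in advance, or use minimisation with a random element on 1-RM and CSA.
- Drop the whole-group re-randomisation step, which cannot operate once participants are allocated one at a time.
- State a maximum interval from 0 W to the start of the intervention, and what happens to the 0 W measurements if it is exceeded before allocation.
- If any batches have already been allocated, document when and how, and include batch as a factor in the mixed model.

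This takes a protocol amendment and a new allocation list, and no additional participants. The downside is that balance on 1-RM and CSA will be slightly looser than ranking the whole cohort at once.

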## Data analysis

Following visual inspection, data normality will be assessed using the Shapiro-Wilk test. In case of normal distribution, a one-way repeated measures analysis of variance (ANOVA) will be implemented to test for differences in baseline values. Then, a mixed model will be applied for each dependent variable (Child-Pugh class, MELD score, SF-36 and FSS scores, dietary records, TUG, 6MWT, SRT, 1-RM, CSA, PA and FL), having group (BFR-RT and CTRL) and time (0 W, 12 W and 24 W) as fixed factors, and participants as random factors. In case of non-normal data distribution, a Kruskal–Wallis test will be implemented to test for differences in baseline values. Then, the Friedman test will be used to analyze repeated measures. To avoid multiplicity interference on data analysis, adjusted *p* values will be calculated for all variables. Adjusted *p* values will be calculated using Hommel’s procedure, and both adjusted and non-adjusted values will be reported. Additionally, within-group (0-12 W and 0-24 W changes) and between-group effect sizes will be calculated using Cohen’s *d* [33] for each outcome. Finally, the minimal clinically important difference will be analyzed with distribution-based methods [34]. Statistical analysis will be carried out using SAS 9.3 software (SAS institute Inc., Cary, NC).

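### Redrawing the allocation until a baseline t test is non-significant does not ensure balance, and the planned model omits the quartile stratification that does most of the balancing

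*Protocol article*

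**What the plan says.** Under Randomization, the whole sample is pooled and sorted into quartiles on baseline 1-RM and CSA. Allocation is then made within quartile: "participants in each quartile will be allocated to either the training (BFR-RT) or control group (CTRL) using a maximally tolerated imbalance model".

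Two further sentences add a screening step. The first is "An unpaired T test will be applied to ensure no baseline difference between groups". The second sets out what follows when that test is positive: "If significant between-groups differences are detected, the randomization procedure will be repeated until a random distribution with no significant difference is achieved".

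Under Data analysis, baseline is tested again. For normally distributed data, a one-way repeated measures ANOVA "will be implemented to test for differences in baseline values"; otherwise a Kruskal–Wallis test is used. The main model is then a mixed model for each of twelve listed variables, "having group (BFR-RT and CTRL) and time (0 W, 12 W and 24 W) as fixed factors, and participants as random factors". The section names no quartile factor, no baseline covariate and no randomization test.

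**The concern.** There are three separate problems.

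- **The rule cannot do what it is said to do.** In a trial of 30, a non-significant t test shows that the test is insensitive. It does not show that the arms are alike.
- **The later baseline tests add nothing.** For any variable already screened, non-significance was forced. The named test is also the wrong kind: a repeated measures ANOVA needs several measurements per participant, and a 0 W value is one measurement per participant.
- **The allocation is restricted but the stated model does not reflect it.** Quartiles and redraws both make the arms more alike on 1-RM and CSA than free randomization would. A test that ignores this uses a standard error that is too large for any contrast correlated with those variables.

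What is at stake is power in a small trial that also applies Hommel's adjustment, and the ease of defending an allocation that may be drawn more than once.

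**Working it through.** The article gives no figure to reproduce on this point.

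**Inputs.** From the article: 30 participants in two arms, quartiles on 1-RM and CSA, a maximally tolerated imbalance procedure within quartile, redraw until non-significant. Assumed, because the article does not state them: 15 per arm; two-sided 0.05 (range 0.01 to 0.10); the t test covers 1-RM and CSA; quartiles formed on a composite of the two; big stick allocation with a maximum imbalance of 2; baseline to follow-up correlation of 0.5 to 0.9.

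**1. Largest baseline difference that passes.** The limit is t(0.975, 28) × √(2/15) = 2.048 × 0.365 = 0.748 SD. At 0.10 it is 0.62 SD and at 0.01 it is 1.01 SD. An observed difference of 0.5 SD gives t = 0.5/0.365 = 1.37, p = 0.18. One of 0.7 SD gives t = 1.92, p = 0.065. Both are accepted.

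**2. What the loop adds to the quartiles.** Simulation under no treatment effect, 6,000 runs per setting, 1-RM/CSA correlation 0.5:

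| Allocation | First draw rejected | Mean absolute 1-RM difference | Share above 0.5 SD |
|---|---|---|---|
| Simple, no loop | – | 0.29–0.30 SD | 17–18% |
| Simple, loop | 9% | 0.26 SD | 12% |
| Quartiles, no loop | – | 0.20 SD | 4.8–4.9% |
| Quartiles, loop | 0.7–1.0% | 0.20 SD | 4.5–4.6% |

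With 1-RM/CSA correlation 0.7, separate simulations gave redraw rates of 0.15% to 0.5%. The quartiles provide the balance and the loop hardly ever fires.

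**3. Type I error at nominal 5%, quartile allocation, outcome 1-RM** (same simulation; correlation 0.5 / 0.8 / 0.9; simulation error about 0.3 percentage points):

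| Test | Without loop | With loop |
|---|---|---|
| Follow-up values only | 3.8 / 1.8 / 1.1% | 3.5 / 1.7 / 0.7% |
| Change from baseline | 3.7 / 4.2 / 5.0% | 3.5 / 4.8 / 4.8% |
| ANCOVA on own baseline | 4.9 / 5.0 / 5.2% | 5.1 / 5.2 / 5.0% |

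**4. Closer to the stated model.** Random-intercept mixed model, quartiles, 1-RM/CSA correlation 0.7, correlation between time points 0.6 / 0.8:

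| Test | Without loop | With loop |
|---|---|---|
| Group-by-time | 4.2 / 4.4% | 4.1 / 4.2% |
| Group main effect | 1.0 / 0.5% | 0.9 / 0.3% |

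In both tables the two columns are much the same. The shortfall from 5% is therefore due to the unmodelled quartiles, and adjusting for baseline removes it.

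**5. Baseline tests.** With two arms, a between-group one-way ANOVA of a 0 W value gives F = t², which is the t test already forced to be non-significant. The repeated measures form has no within-participant factor at a single time point.

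**The case against.** The strongest defence is that the mixed model already contains 0 W as a level of time. The outcome's own baseline is thus in the model as a response, and a group-by-time contrast behaves like a change score. That stands: the contrast runs at about 4%, and the redraw does not move it beyond simulation error. What is absent is a baseline covariate and a stratum term, which is a smaller gap than ignoring baseline altogether. The article lists group and time as fixed factors without writing out the interaction, so the size of the loss depends on which contrast is used.

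A second defence is that a rule which almost never fires can do little harm. That also stands, but it is equally a reason to remove the rule.

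Several stronger readings are tempting and are not supported:

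- **Inflated false positives.** Every departure found is in the conservative direction.
- **The redraw as the cause of the lost power.** The figures without the loop are nearly the same.
- **Frequent redraws.** A reader might infer that the t test covers all twelve variables in Data analysis. The Randomization section names only 1-RM and CSA, and the twelve include a categorical one (Child-Pugh class).
- **Discretion to reject an unwelcome allocation.** The text gives a mechanical significance rule. Its level, variable list and any cap on repeats may be in the full protocol.
- **A worthless selection-bias check.** The article says "The Berger-Exner test will be performed during data analysis to verify for selection bias". Single-draw allocation probabilities would not exactly describe a redrawn list, but with redraws this rare they would barely change, and no failure of the test has been shown.

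**Conclusion.** The point holds as a design and analysis correction, not as a threat to the validity of a positive result. The redraw rule does not ensure balance, since it accepts differences up to about 0.75 SD with 15 per arm at 5%. On top of quartile allocation it changes almost nothing. The baseline tests in Data analysis serve no purpose, and one of them is the wrong kind of test.

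The larger cost is that the stated model omits the stratification. That cost is lost power: severe for a 12 W-only comparison or a group main effect, slight for a group-by-time contrast. These sizes rest on the assumed equal arms, composite quartiles, imbalance limit and correlations. The direction and the ordering of the tests were the same in every setting tried.

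**What to change.** - Delete the redraw rule and all baseline significance tests (unpaired t, one-way repeated measures ANOVA, Kruskal–Wallis).
- Make one computer-generated, logged, stratified allocation, and show baseline by arm descriptively.
- Base the between-arm contrasts on a model of the 12 W and 24 W values, adjusted for the outcome's own 0 W value and for the stratifying variables (quartile, or baseline 1-RM and CSA). Alternatively, keep 0 W as a response in a mixed model that constrains the arms to a common baseline mean, and add the stratum term. The 0 W value should not be both a response level and a covariate in the same model, so this changes the model's structure as well as its wording.
- Trial status reports that recruitment was still open at submission. If a redraw has nevertheless been made, report how many and the acceptance rule, and add a re-randomization test that replays that rule.

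The cost is a few degrees of freedom in a trial of 30, and a chance imbalance that may be visible in the baseline table, for which the model then adjusts.
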